### Statistical analysis

#### Sample size calculation and power considerations

In order to show a difference in the proportion of participants achieving a high composite lifestyle score from 30% in the control arm to 50% in the study arm after 24 weeks of the intervention, with 80% power at a *P* value of < 0.05, 93 patients will be required in each arm. We have assumed a randomisation rate of 50% and assuming a drop-out rate of 15–20%, 220 patients will be randomized to each arm (440 patients to be recruited in total).

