#### Data analysis

The difference between two groups for the composite score will be expressed as a proportion of those achieving high scores at the end of the intervention period. Chi squared testing will be applied to test these categorical variables for significance. Differences in parameters will be tested by a two-tail Mann Whitney U test. In order to adjust for predefined confounders such as age, socioeconomic class, educational attainment, working status and ethnicity, multiple regression analysis will be performed.

Missing data will be described, for example, by presenting the number and percentage of individuals in the missing category. All data collected on collection forms will be used, since only essential data items will be collected. No data will be considered spurious in the analysis since all data will be checked and cleaned before analysis. Range checks, identification of extreme values (Mean +/− 3*Std Dev) and consistency checks will be used to identify possible data errors.

An intention to treat analysis will be performed. No interim analysis is planned.

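### The printed target of 220 randomised per arm does not follow from the plan's own inputs, which give 110 to 117 per arm

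*Protocol article*

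**What the plan says.** All the figures are in the protocol article, section *Sample size calculation and power considerations*.

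- Effect: the proportion with a high composite lifestyle score is to rise "from 30% in the control arm to 50% in the study arm", assessed at 24 weeks.
- Evaluable number: "with 80% power at a *P* value of < 0.05, 93 patients will be required in each arm".
- Allowances: "We have assumed a randomisation rate of 50% and assuming a drop-out rate of 15–20" per cent.
- Conclusion: "220 patients will be randomized to each arm (440 patients to be recruited in total".

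The randomisation rate is not defined. The sections *Study population and recruitment* and *Randomisation* place consent, account registration and the baseline questionnaire before allocation, so the number recruited can exceed the number randomised. No other section gives a different sample size or a reason for a larger trial.

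**The concern.** The step from 93 to 220 per arm is far larger than a 15–20% drop-out allowance can produce. The conclusion also conflicts with the assumption just before it. Two arms of 220 make 440, so every recruited woman would be randomised. That leaves no room for a 50% randomisation rate, if the rate means the share of recruited women who go on to be randomised.

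At stake is the size of the trial. A reader cannot tell whether about 220 or 440 women are to be randomised. Feasibility, the end of recruitment and any later judgement of whether the target was met depend on that number. No interim analysis is planned that might revisit it.

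**Working it through.** **Inputs.** From the sample size section: p1 = 0.30, p2 = 0.50, power 80%, alpha 0.05, drop-out 15–20%, randomisation rate 50%. Sidedness is not stated there. Two-sided is assumed because the *Data analysis* section names a chi-squared test and because it reproduces the printed 93 (one-sided gives 74).

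**1. Reproduce the plan's 93.** Mean proportion = 0.40.

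n = [1.96 × √(2 × 0.40 × 0.60) + 0.8416 × √(0.30 × 0.70 + 0.50 × 0.50)]² / 0.20²
= [1.358 + 0.571]² / 0.04 = 93.0 per arm.

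This agrees with the printed figure.

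**2. Add drop-out, n / (1 − d), and then the randomisation rate.**

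| | 15% drop-out | 20% drop-out |
|---|---|---|
| Randomised per arm | 93 / 0.85 = 109.4, so 110 | 93 / 0.80 = 116.25, so 117 |
| Randomised in total | 220 | 234 |
| Recruited at 50% | 220 / 0.5 = 440 | 234 / 0.5 = 468 |

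The 15% column contains both printed numbers, but with 220 as a total. Applying both allowances within one arm gives 93 / (0.85 × 0.5) = 218.8. That is about 220 again, but it counts women recruited per arm, not randomised. Either route leaves 110 randomised per arm.

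**3. Test the printed 220 per arm directly.** Falling from 220 to 93 would need a loss of 1 − 93/220 = 58%, against the stated 15–20%.

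**4. Try other methods.** The continuity-corrected formula gives 103 per arm, hence 122 at 15% and 129 at 20% drop-out. The arcsine method gives 93. None approaches 220.

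**5. Power for 30% versus 50% under each meaning of 220.**

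Power = Φ{[0.20 × √n − 1.358] / 0.678}, where 0.678 = √(0.21 + 0.25) and n is the evaluable number per arm.

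| Randomised per arm | Drop-out | Evaluable per arm | Power |
|---|---|---|---|
| 110 | 15% | 93.5 | 80.2% |
| 110 | 20% | 88 | 77.8% |
| 220 | 15% | 187 | 97.9% |
| 220 | 20% | 176 | 97.2% |

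With 176–187 evaluable per arm, 80% power corresponds to about 30% versus 44%.

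**The case against.** **The randomisation rate might mean 1:1 allocation.** The term is undefined, and on that reading the conflict with 440 recruited disappears. This stands: the contradiction is conditional on the rate being the share of recruited women randomised. It does not rescue 220, because 93 is already a per-arm figure and doubling it would count the allocation twice.

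**The sponsor may simply want a larger trial.** That is possible, but the article gives no such reason and presents 220 as the result of the stated rates.

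**A reader might infer that the plan claims 80% power for 220 per arm.** It does not. The 80% is attached to 93 per arm, where it is correct. The fault lies in the step after that.

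**A reader might infer that the trial is underpowered.** The document does not support this. Taken literally, the size gives 97–98% power. If 220 is the total, the shortfall is about 2 percentage points, and only at the upper end of the drop-out range.

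**A reader might take 220 as certainly a misprinted total.** The match at 15% is strong evidence, but it is an inference. The match fails at 20%, and only the sponsor knows what was intended. For the same reason, the arithmetic alone does not justify halving the target. The calculation also concerns a dichotomised score at 24 weeks, while the primary endpoint is the composite score at 12 weeks.

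**Conclusion.** The point holds as a derivation error in the printed target. From correct evaluable numbers, the stated drop-out gives 110–117 randomised per arm, and no reading of the stated inputs gives 220. The most likely explanation is a total printed as a per-arm figure. The consequence is a twofold ambiguity in the number to be randomised, and a size that does not match its stated power basis. The comparison between arms is not biased by it.

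This rests on a two-sided test, the pooled-variance formula that reproduces 93, and drop-out counted as loss after randomisation. The recruited figures further assume that the 50% rate is the share of recruited women who are randomised. The 110–117 per arm does not depend on that last assumption.

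**What to change.** Define the randomisation rate, state whether 220 is per arm or in total, and restate the paragraph accordingly.

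- **If 220 is the total:** state 110 randomised per arm from 440 recruited, with power of 80% at 15% drop-out and 78% at 20%. Keeping 80% power at 20% drop-out would correspond to 117 per arm, 234 randomised and 468 recruited. That is 14 more randomised and 28 more recruited than 220 and 440.
- **If 220 per arm is intended:** keep it, remove the 50% rate from the derivation, and state that 176–187 evaluable per arm give 97–98% power for 30% versus 50%, or 80% power for about 30% versus 44%.

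The cost is a rewording of one paragraph, unless the sponsor chooses to cover 20% drop-out at 80% power. The target in the trial registration is not shown in the article and should be checked for consistency.

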#### Data analysis

The difference between two groups for the composite score will be expressed as a proportion of those achieving high scores at the end of the intervention period. Chi squared testing will be applied to test these categorical variables for significance. Differences in parameters will be tested by a two-tail Mann Whitney U test. In order to adjust for predefined confounders such as age, socioeconomic class, educational attainment, working status and ethnicity, multiple regression analysis will be performed.

Missing data will be described, for example, by presenting the number and percentage of individuals in the missing category. All data collected on collection forms will be used, since only essential data items will be collected. No data will be considered spurious in the analysis since all data will be checked and cleaned before analysis. Range checks, identification of extreme values (Mean +/− 3*Std Dev) and consistency checks will be used to identify possible data errors.

An intention to treat analysis will be performed. No interim analysis is planned.

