### Primary and secondary endpoints

The primary endpoint of the study is the composite dietary and lifestyle risk score at 12 weeks after randomisation. Secondary endpoints include (i) percentage of patients remaining compliant with system at 12, 18 and 24 weeks after randomisation, (ii) proportion achieving spontaneous conception during study period and (iii) composite dietary and lifestyle risk score at 24 weeks after randomisation.

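### The primary endpoint is the composite score at 12 weeks, but the analysis named for it is a chi-squared test on the proportion with a high score at the end of the intervention

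*Protocol article*

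**What the plan says.** Primary and secondary endpoints: "The primary endpoint of the study is the composite dietary and lifestyle risk score at 12 weeks after randomisation". The abstract agrees. Neither place gives a cut-off or a responder definition. The same score at 24 weeks is listed as a secondary endpoint.

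Data analysis: the between-group difference for the composite score "will be expressed as a proportion of those achieving high scores at the end of the intervention period", followed by "Chi squared testing will be applied to test these categorical variables for significance". The next sentence reads "Differences in parameters will be tested by a two-tail Mann Whitney U test", without saying which parameters are meant. A multiple regression for predefined confounders follows, without naming the outcome to which it applies.

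Sample size calculation and power considerations: the trial is sized on the same dichotomy, namely the proportion "achieving a high composite lifestyle score from 30% in the control arm to 50% in the study arm after 24 weeks of the intervention", giving "93 patients will be required in each arm". The section then states 220 randomised to each arm and 440 in total, assuming a 50% randomisation rate and 15-20% drop-out.

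**The concern.** The only comparison that the article explicitly assigns to the composite score is a comparison of proportions. A woman whose score improves substantially without crossing the cut counts the same as one who did not change, and a woman who crosses it by the smallest step counts as a full success. The trial asks whether coaching improves behaviours, which the score measures more directly than a cut does.

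Two things are at stake. The declared primary endpoint and the analysis that will be reported for it may not be the same quantity. And cutting a graded score usually costs power and precision.

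The three sections also disagree on other features of the endpoint. The endpoint is at 12 weeks, the sample size refers to 24 weeks, and the analysis refers to the end of the intervention period. The endpoint is named a risk score, while the sample-size section treats a high lifestyle score as the better result.

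**Working it through.** **Inputs from the sample-size section.** High score in 30% (control) and 50% (intervention); "with 80% power at a" significance level given as a P "value of < 0.05"; 93 per arm. Sidedness is not stated. Two-sided is assumed, and it reproduces the stated figure.

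**1. The plan's own figure.** Two proportions, pooled variance under the null, no continuity correction:

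n = [1.960 × √(2 × 0.40 × 0.60) + 0.842 × √(0.30 × 0.70 + 0.50 × 0.50)]² / 0.20² = 93.0 per arm.

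The stated 93 is reproduced. A continuity correction would give 103.

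**2. Same effect, score analysed as a score, normal shift (assumption).** If the score is roughly normal and the intervention shifts it by a constant amount, 30% against 50% above one cut corresponds to

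d = z(0.50) − z(0.30) = 0.524 SD.

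- Comparison of means: n = 2 × (1.960 + 0.842)² / 0.524² = 57.1 per arm. Loss from the cut: 1 − 57.1/93 = 39%.
- Mann-Whitney, relative efficiency 3/π: 57.1 × π/3 = 59.8 per arm. Loss: 1 − 59.8/93 = 36%.

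Rounding up to whole patients adds about one per arm and leaves the loss at 35-38%.

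**3. Same effect, proportional-odds shift (alternative assumption).** The odds ratio is (0.50/0.50)/(0.30/0.70) = 2.33.

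- Continuous score, Noether's formula: the probability that an intervention score exceeds a control score is 0.638, so n = 7.849/(6 × 0.138²) = 68.8 per arm, where 7.849 = (1.960 + 0.842)². Loss: 26%.
- Ordered categories, Whitehead's formula, n = 6 × 7.849 / [(ln 2.33)² × (1 − Σp̄³)], where p̄ is the mean proportion in each category. The control-arm distributions are illustrative.

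| Score levels | n per arm | Loss against 93 |
|---|---|---|
| 10 | 66.4 | 29% |
| 5 | 68.4 | 26% |
| 3 | 74.5 | 20% |

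The loss therefore ranges from about 20% to 39%.

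**4. Power at the numbers likely to be evaluable.** The recruitment figures allow two readings.

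- *220 per arm randomised, as written.* After 15-20% drop-out, 187-176 per arm are evaluable. Chi-squared power is 98-97%. Analysing the score gives above 99% under either assumption.
- *440 approached and 220 randomised in total.* This reading fits the stated inputs: 2 × 93 = 186, and 186/0.5/0.85 = 438. With 110 per arm randomised, 93.5-88 are evaluable. Chi-squared power is 80-78%. A comparison of means under normality gives Φ(0.524 × √(93.5/2) − 1.960) = 95% and, at 88, 94%. Mann-Whitney gives 94-92%. Under proportional odds the score gives about 86-91%.

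All these figures use the 30% and 50% that the article gives for 24 weeks. It gives no expected effect at 12 weeks.

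**The case against.** **The score may be compared after all.** A reader might infer that the declared endpoint is never tested. The text does not support that. The Mann-Whitney sentence could cover the composite score, because the parameters are not defined. What stands is that this test is not tied to the primary endpoint, whereas the preceding sentences assign the composite score to a proportion and chi-squared. At best there are two candidate primary tests.

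**Adjustment is planned.** It would be wrong to describe the analysis as simply unadjusted, since a multiple regression for confounders is named. It is not linked to any outcome, and the baseline score is not among the examples of covariates.

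**The loss may be under a third.** It is tempting to say that the cut discards over a third of the information. That holds under a normal shift, but not under proportional odds. The article gives no range, SD or number of levels, so only the wider range is defensible.

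**Power may be ample.** At 220 per arm as written, it is. The argument from power then has little force, although the mismatch in definition is unaffected by sample size.

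**The cut may be fixed elsewhere.** A reader might infer that the threshold could be chosen after the data are seen. A journal article commonly leaves such detail to the full protocol or SAP, neither of which is shown, so its absence here is not evidence that it is open.

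**The sample-size and analysis sections agree.** Both use the dichotomy, so a responder comparison was evidently intended. That is fair, but both then depart from the endpoint section.

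**Conclusion.** The concern holds in this limited form. The primary endpoint is a score at 12 weeks, and the analysis explicitly named for that score is a chi-squared comparison of the proportion with a high score at the end of the intervention period, which the sample-size wording suggests is 24 weeks. The other methods named are not connected to the primary score.

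The statistical cost of the cut is about 20-39% of the information, resting on an assumed shift model. The gain in power is material if about 88-94 per arm are evaluable (78-80% to 94-95% for means under normality, less under proportional odds) and small if 220 per arm are randomised. The inconsistency between endpoint and analysis does not depend on any of these assumptions. It should be corrected.

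**What to change.** In Data analysis, name one primary comparison: the between-arm difference in the composite score at the declared primary time point (12 weeks, unless the endpoint section is changed), with a 95% confidence interval, from a linear regression adjusted for the baseline score, which is already collected. If the score has few levels, use a proportional-odds model or the Mann-Whitney test already named. Keep the proportion with a high score, at a pre-specified cut, as a supportive summary.

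Align the endpoint, sample-size and analysis sections on the time point and on whether a high score is favourable. The 93-per-arm calculation can stay as a conservative basis if it is labelled as resting on the dichotomy. If the sponsor prefers the proportion as primary, the minimum is to redefine the primary endpoint to match.

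No additional data are needed. A mean difference is less readable than a percentage, which is why the percentage stays as supportive, and the sample-size text needs a sentence of explanation.

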**Fig. 1 Fig1:**
[figure not shown]
Flow diagram for the iPLAN study design

Women from both intervention and control group will be asked to visit the ‘Smarter Pregnancy’ website (www.smarterpregnancy.org.uk) and will be asked to register and activate their account by a unique validation code. Women will be asked to complete a baseline lifestyle questionnaire which assesses parameters including smoking habits, alcohol consumption, diet, exercise and weight, and then will be randomised by the ‘Smarter Pregnancy’ computer programme to either intervention arm or control arm. Both intervention and control group login to ‘Smarter Pregnancy’ using their personalised credentials created at registration.

In the intervention arm, women will have access to a personalised smartphone lifestyle coaching program. Through baseline and follow up lifestyle questionnaires (at 6, 12, 18 and 24 weeks) sent out via email, tailored lifestyle advice is generated; emails with tips, facts and recipes are sent to the intervention arm participants to encourage them to change unhealthy habits and maintain healthy habits. Coaching is focussed on study subjects who report inadequate intake of vegetables and fruit, and absence of folic acid supplementation, and those with unfavourable alcohol and smoking habits, which are identified by the baseline and follow up questionnaires. The smartphone application allows the women to update their pregnancy status; if the subject is pregnant, lifestyle advice is adapted for the pregnancy. Those randomised to the control arm will have access to standard periconceptional advice, including information from NHS websites.

The results will be analysed to determine whether a smartphone lifestyle coaching application can improve lifestyle behaviours in the periconceptional period, through a validated lifestyle questionnaire (see Appendix 1) at 6, 12, 18 and 24 weeks after randomisation. Patient compliance with the system at specific time points (at 6, 12, 18 and 24 weeks after randomisation) and the proportion of women achieving spontaneous conception during the study period will also be assessed. The expected length of time each subject will participate in the study for is 6 months after randomisation.

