### Randomisation

Participating women will be randomised in program by the computer generation of a series of validation codes which is unique for each participant. After completion of the baseline questionnaires, women will be randomised to the intervention or the control group. The randomisation process will be concealed and the research team will be blinded to the randomisation.

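### The baseline composite score, available for every randomised woman, is not named in the analysis; adding it as a covariate would gain precision at no data cost, although the unadjusted test is valid

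*Protocol article*

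**What the plan says.** **Baseline measurement.** The Study design section (text after Fig. 1) says: "Women will be asked to complete a baseline lifestyle questionnaire which assesses parameters including smoking habits, alcohol consumption, diet, exercise and weight". The Randomisation section fixes the order: "After completion of the baseline questionnaires, women will be randomised to the intervention or the control group". Under Data collection, the same validated questionnaire is repeated at 6, 12, 18 and 24 weeks.

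**Analysis.** The Data analysis section expresses the arm difference as the proportion with high scores at the end of the intervention and tests it by chi-squared. Other parameters are compared by a two-tailed Mann-Whitney U test. The adjusted analysis is described in one sentence: "In order to adjust for predefined confounders such as age, socioeconomic class, educational attainment, working status and ethnicity, multiple regression analysis will be performed". The baseline score is not named there, and no analysis of change from baseline is described.

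**Sample size.** The calculation is for a binary outcome, "from 30% in the control arm to 50% in the study arm after 24 weeks of the intervention". The significance level is 5% and the target power 80%. It concludes that "93 patients will be required in each arm". After a 50% randomisation rate and "assuming a drop-out rate of 15–20" per cent, it states that "220 patients will be randomized to each arm (440 patients to be recruited in total".

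**The concern.** An earlier measurement of the outcome score is likely to be a strong predictor of the later one. By design it is complete at allocation and unaffected by treatment, so it is a natural first covariate. The article instead names age, social class, education, work and ethnicity, and calls them confounders. In a randomised comparison these are prognostic covariates, and their purpose is precision.

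Two features of the design make the starting level relevant. The Study population and recruitment section requires no unhealthy behaviour at entry, so a woman who already scores high and stays high counts as a success in either arm. The coaching is directed at women whose questionnaires show inadequate intake or unfavourable habits. The outcome therefore mixes women who improved with women who had little to improve.

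What is at stake is efficiency: a less precise estimate than the collected data allow, and a result that can be moved by a chance difference in starting lifestyle between the arms.

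**Working it through.** **1. Inputs.** From the Sample size section: 30% v 50% with high scores, 80% power, P < 0.05, 93 per arm, 220 per arm randomised, drop-out 15–20%. Assumed, because the documents give no value: baseline-to-follow-up correlation r = 0, 0.3, 0.5, 0.7.

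**2. Reproducing the plan's figure.** Pooled-variance formula, two-sided, no continuity correction, with mean proportion 0.40:

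n = [1.96 × √(2 × 0.40 × 0.60) + 0.842 × √(0.30 × 0.70 + 0.50 × 0.50)]² / 0.20² = (1.358 + 0.571)² / 0.04 ≈ 93.

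The stated 93 is reproduced, so the sample size arithmetic is not at issue here.

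**3. Adding the baseline score to the binary analysis.** The simulation used 93 per arm and 3,000 replicates per scenario. A normal underlying score was cut so that 30% v 50% score high, which corresponds to a shift of z(0.50) − z(0.30) = 0.524 SD. The baseline score correlates r with follow-up. Each data set was analysed by chi-squared and by logistic regression on arm and continuous baseline score.

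| r | Power, chi-squared | Power, logistic + baseline | Type I error, chi-squared | Type I error, logistic + baseline |
|---|---|---|---|---|
| 0 | 79.9% | 79.6% | 4.6% | 4.0% |
| 0.3 | 80.1% | 82.1% | 5.4% | 5.4% |
| 0.5 | 79.2% | 85.8% | 5.2% | 4.9% |
| 0.7 | 80.3% | 91.7% | 5.7% | 4.7% |

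Monte Carlo standard error near 80% is √(0.8 × 0.2 / 3000) = 0.7 points. A repeat of the simulation gave about 82%, 87% and 93%, hence the ranges 82%, 86–87% and 92–93%.

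**4. Expressed as women per arm.** The formula in step 2 gives the unadjusted number needed for those powers, with z(power) in place of 0.842:

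- 82%: (1.358 + 0.915 × 0.678)² / 0.04 ≈ 98
- 86–87%: (1.358 + 1.080 × 0.678)² / 0.04 ≈ 109, up to (1.358 + 1.126 × 0.678)² / 0.04 ≈ 113
- 92–93%: (1.358 + 1.405 × 0.678)² / 0.04 ≈ 134, up to (1.358 + 1.476 × 0.678)² / 0.04 ≈ 139

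In round terms, 93 adjusted women per arm are worth about 98, 110 and 135 unadjusted.

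**5. Dependence on the number actually randomised.** Unadjusted power with m evaluable per arm is Φ[(0.20√m − 1.358) / 0.678].

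- 220 per arm randomised: 220 × 0.80 = 176 gives 97.2%; 220 × 0.85 = 187 gives 97.9%.
- The stated 50% randomisation rate could instead mean that 220 is a count before that loss, since 93 / (0.50 × 0.85) = 219. About 110 per arm would then be randomised, leaving 88 (110 × 0.80) to 94 (110 × 0.85 = 93.5) evaluable, with power of about 78–80%.

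**The case against.** **The list of covariates is open.** The words introducing it are illustrative, so the baseline score is unnamed and not excluded. A reader might infer that the plan rejects baseline adjustment, and the text does not say so. Nor does it say whether the Mann-Whitney comparisons use follow-up values or changes. A complete covariate list, and which model decides, are matters that an article may leave to the full protocol or analysis plan. This stands. What remains is that the article does state its test and its kind of covariate, and the stated choice can be improved.

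**The unadjusted test is valid.** A reader might infer that ignoring baseline, or counting women who were already high, biases the result. It does not. Such women are expected equally in both arms, chance imbalance is covered by the test's error rate, and simulated type I error was 4.0–5.7% with or without baseline. This stands in full.

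**The gain may be negligible.** With 220 per arm truly randomised, power for 30% v 50% is already about 97–98%. This stands on that reading. It does not stand if about 110 per arm are randomised, and a true difference below 20 points would also make the gain matter.

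**Baseline may be a weak predictor.** The documents report no correlation. They do not support calling the baseline score the strongest predictor, or saying that the sociodemographic factors act mainly through it. It is only likely to be a strong one.

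**Conclusion.** The point holds as an efficiency recommendation. At 93 per arm, naming the baseline score would raise power from about 80% to about 82%, 86–87% or 92–93% under assumed correlations of 0.3, 0.5 or 0.7. With no correlation there is no gain. The calculation assumes a normal underlying score and the plan's 30% v 50%.

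Two larger figures are tempting and should not be used. Dividing 93 by 1 − r² gives 102, 124 and 182 per arm, but that factor applies to a continuous score analysed by ANCOVA, whereas 93 was derived for a high/low outcome. Likewise, the fall from 93 to 58 per arm at r = 0 when the score is analysed as continuous comes from not dichotomising. That is a separate question.

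**What to change.** In the Data analysis section, name the baseline composite score, in continuous form, as a prespecified covariate in the regression already planned, and close the list of other covariates. Make the baseline-adjusted arm effect the primary result: logistic regression if the high/low outcome is kept, ANCOVA if the score is analysed as continuous. Keep the chi-squared test as a supportive analysis.

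With the high/low outcome kept, this is a sentence or two of wording. It needs no new data, because the questionnaire precedes randomisation, and 93 per arm remains a conservative number. Moving to a continuous score would cost more, because the sample size rests on the binary comparison and would have to be restated. This recommendation does not depend on that move.
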